## Abstract

**Background:**

Cardiac rehabilitation (CR) programs have shown promising results in tertiary prevention. However, achieving sustained behavioral changes remains a challenge.

**Objective:**

The TIMELY project aims to develop and evaluate a personalized, artificial intelligence–driven eHealth platform and app to support sustainable behavior change during phase-3 CR, subsequently reducing cardiac risk scores.

**Methods:**

An international, multicenter, randomized controlled trial will be conducted to evaluate the effectiveness of the TIMELY integrated platform and app. A total of 360 patients with cardiac conditions will be approached to participate in the study across Germany, Spain, and the Netherlands. Patients will be randomly assigned (1:1) to either the intervention group or the control group (care as usual). The intervention group will receive fully web-based, behavior change support through the TIMELY app, with personalized exercise prescription, chatbot assistance, and monitoring devices (eg, activity watch). Both groups will continue to receive care as usual, complete validated questionnaires, undergo physical tests, and provide blood samples. Assessments will be conducted at baseline and at 3, 6, and 12 months.

**Results:**

Trial recruitment has been finalized in July 2024. A total of 358 patients have been recruited and randomly assigned to the intervention (n=180, 50.1%) or care-as-usual (n=178, 49.7%) condition. As of January 2025, the 6-month follow-up has been completed for all participants. Follow-up data collection will be completed in May 2025. Results regarding the primary and secondary objectives are expected in September 2025.

**Conclusions:**

This project will test a personalized platform and app, supported by artificial intelligence and designed to support health behavior change during phase-3 CR. It will target multiple health behaviors, with a primary focus on physical activity and fitness levels, using an integrated approach.

**Trial Registration:**

ClinicalTrials.gov NCT05955625; https://clinicaltrials.gov/ct2/show/NCT05955625

**International Registered Report Identifier (IRRID):**

DERR1-10.2196/66283

## Introduction

### Background

Cardiovascular diseases are the leading cause of death worldwide, accounting for approximately 17 million deaths annually [1]. Improvements in cardiac treatment over the past decades have increased the number of people surviving cardiac events and living with cardiac disease. Consequently, cardiac disease management and tertiary prevention of adverse outcomes such as recurrent cardiac events or mortality have become increasingly important in clinical practice and patients’ lives [2]. Cardiac rehabilitation (CR) programs play an important role in this risk factor management and have been demonstrated to improve patient outcomes effectively [3].

### Cardiac Rehabilitation

The World Health Organization defines CR as “the sum of activities required to influence favorably the underlying cause of the disease, as well as to provide the best possible physical, mental, and social conditions, so that the patients may, by their own efforts, preserve or resume when lost as normal a place as possible in the community” [4]. CR is a guideline-recommended [5], multidisciplinary, multimodal tertiary prevention program consisting of modules that include exercise training, optimization of medical treatment and risk factor management, smoking cessation, heart-healthy dietary habits, risk factor education, and psychosocial counseling [6,7]. Phase 1 is the inpatient care that is characterized by the implementation of modern acute coronary revascularization techniques as well as the application of effective acute and long-term pharmacotherapy aiming at early mobilization of the patient after a cardiac event or surgery. This phase is followed by phase-2 CR, which typically addresses patient’s personal risk factor modification by adopting a healthy lifestyle. This represents the most important challenge, often described as the intention-behavior gap. Changes achieved during phase 2 are aimed at being consolidated in phase-3 CR. Long-term maintenance of health behavior changes after CR (ie, during phase-3 CR) varies substantially in the level of support offered to patients [8]. In most countries, the availability of phase-3 CR support is limited because of reimbursement policies. When center-based support is offered, only a small subgroup of patients attends these sessions, often due to a lack of personalized guidance and logistical challenges such as time constraints and travel burden [9,10]. These patient- and health system–related barriers contribute to low adherence to and uptake of long-term rehabilitation and cardiovascular health maintenance programs despite their potential health benefits [11,12]. Therefore, it is of utmost importance to explore delivery modes for long-term CR maintenance that better align with the needs of both patients and healthcare providers, while addressing existing barriers.

### eHealth in CR

Web-based care modalities for CR might be the way forward to address the challenges associated with “traditional” in-person CR. These modalities offer the opportunity to provide *personalized care* or support to patients at their convenience, while also being *scalable* and *cost-effective* [13-15]. Such an approach should include both a continuous risk analysis by monitoring multiple disease-related prognostic parameters as well as regular support and guidance for a cardiac healthy lifestyle. A recent meta-analysis by Heimer et al [16] demonstrated that eHealth-based, phase-3 CR is effective in increasing exercise capacity, improving quality of life, and decreasing blood pressure (BP). Another meta-analysis found that remote CR is associated with better behavioral, psychosocial, and health service use outcomes [13,17]. These findings suggest that technological innovations can help develop a continuum of care after initial center-based CR to sustain its benefits and improve health outcomes. Therefore, recent studies have focused on the development of behavioral interventions to support long-term CR maintenance [18-20].

### Cardiac Healthy Behavior Change

Developing and maintaining a cardiac-healthy lifestyle is of utmost importance to improve prognosis and reduce mortality risk in people with cardiac disease. It has been demonstrated by multiple studies [21,22] and advocated by others [23,24] that health behaviors, and in particular physical activity, should be addressed to improve cardiac health. Changing health behavior is a challenging endeavor, and only few people succeed [25]. Particularly, patients who face complicated disease regimen or adjustment problems (psychological or psychosocial) due to their illness (such as coronary artery disease [CAD]) may experience health behavior change as burdensome. This is also reflected by the typically temporary nature of the changes in health behavior that do not persist in the long term [26]. To promote sustainable behavior change, the application of behavior change techniques (BCTs) has been advocated [27]. The current literature indicates that a variety of BCTs may be implemented in CR programs to enhance their effectiveness. The TIMELY consortium conducted 2 studies that guided the development of the TIMELY intervention, 1 focusing on the patient perspective (qualitative) [28] and 1 evaluating existing literature through a systematic review [29]. Triangulating the findings from the studies revealed that specific BCTs can be successfully implemented to improve health behavior and clinical outcomes when they align with patients’ preferences and are optimally matched with target behaviors.

### TIMELY

To overcome current barriers related to phase-3 CR programs, the TIMELY trial aims to evaluate the cost-effectiveness of a personalized eHealth platform and health behavior change app for patients with CAD. This platform and app will provide support for health behavior change (eg, artificial intelligence [AI]–supported personalized exercise prescription [EP]) and facilitate disease-related self-management based on current clinical guidelines and in accordance with patients’ individual needs. The TIMELY intervention will integrate (through the TIMELY platform) demographic, clinical, and psychosocial data to assess cardiac risk and support patients in maintaining and improving health behaviors via app-based feedback and prompts. Therefore, the TIMELY intervention is designed to preserve the benefits of CR and reduce cardiac risk in patients with CAD. At the same time, this approach reduces the burden on health care providers and the health care system. The TIMELY intervention is the first intervention for patients with CAD to support its users with physical activity and stress management through a chatbot function, and to offer a personalized weekly EP that is adapted based on exercise parameters collected throughout the week [30]. Previous interventions using increasing exercise goals based the goals on single parameters such as baseline activity levels or heart rate reserve, whereas the EP in the TIMELY intervention is based on several medical, demographic, and behavioral parameters [31,32]. Figure 1 shows a graphic outline of the TIMELY approach. It is hypothesized that participants who follow the TIMELY intervention, as compared to care as usual, will have a lower 10-year cardiac risk mortality and improved physical fitness over time. In addition, they are expected to have better physical and mental well-being and quality of life.

**Figure 1 figure1:**
[figure not shown]
The TIMELY approach. AI: artificial intelligence; BCT: behavior change technique; CR: cardiac rehabilitation.

## Methods

### Design

The TIMELY study is an international (Germany, Spain, and the Netherlands), multicenter, randomized controlled trial. Patients randomly assigned to the intervention condition will receive a 6-month, app-based, personalized behavior change intervention. Assessments will be performed at baseline and at 3, 6, and 12 months.

### Ethical Considerations

The TIMELY trial has been registered at ClinicalTrials.gov (NCT05955625) and has been approved by the Medical Ethics Committee (METC-Brabant NL82723.028.22/P2251 Tilburg, protocol V9 24-05-2023, the Netherlands). Local approvals from the participating centers (Germany: Z-125/2023; Spain: CEIm-G 2023/119) have been obtained. Data collection was initiated after receiving a signed informed consent from the participants. Participants have the option to opt out at any time—before, during, or after data collection—in which case their data will be deleted. Data will be pseudonymized, and only the research team from each center will have access to the key list for their center. A data sharing agreement between the participating centers has been signed for sharing pseudonymized data for data analysis purposes. Informed consent covers secondary analysis without additional consent. Participants were not reimbursed for participation except for study-related expenses (eg, parking costs).

### Monitoring

Tilburg University has been appointed as the trial sponsor and will perform regular monitoring of the trial. This includes 2 visits (midterm and closing-out) to the clinical centers in Germany and Spain. During this visit, the investigator site file will be reviewed, and random checks of 20% of the participants regarding clinical data and questionnaires will be performed. Informed consent forms will be checked for all participants. In the Netherlands, the monitoring visits will be performed by an independent researcher from Tilburg University who is not affiliated with the TIMELY trial.

Throughout the study period, monitoring of serious adverse events will be performed per center. If serious adverse events are reported by patients or discovered in the patient record, this will be reported to the sponsor, who will register the events within 1 week at the Dutch Central Committee on Research Involving Human Subjects. The events will also be registered at the German Federal Institute for Drugs and Medical Devices.

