#### TIMELY App

The TIMELY app (available for Android and IOS devices) was developed following a simplistic design approach and serves two central purposes: (1) collecting self-report data or PROMs and (2) providing personalized information (from wearable or monitoring data) and advice regarding health behavior change (Figure 3). To achieve these goals, the app provides seven functionalities: (1) messaging function for nudging and information; (2) ecological momentary assessment diary assessment of symptoms, perceived stress, sleep quality, affective states, social behavior, motivation, and goal setting; (3) lifestyle and health information; (4) chatbot interaction guided by specific counseling techniques and methods; (5) weekly EP; (6) documentation and visualization of physical activity and vital signs; and (7) documentation and visualization of BP. The app was freely available for study participants and could be used by participants at their own time and pace.

The functionalities provided by the app (in combination with the microservices run on TIMELY-Net) are detailed in Textbox 1.

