#### The Role of the TIMELY Case Manager

In alignment with a realistic health care setting, case managers (rehabilitation nurses and health care assistants) will provide technological and app-specific support during the study. During the inclusion period, patients are onboarded by the case manager, which includes giving access to the app and related monitoring devices and ensuring that participants understand the study requirements and all provided functionalities. The case manager sets the first weekly step goal together with the patient, and the patient agrees to the first EP (shared decision-making). Within the first week after inclusion, the case manager will contact the participants to verify proper installation of the app and monitoring devices, ensuring data collection integrity. Participants will have the opportunity to ask questions about the device functionality. During the intervention period (6-month follow-up), patients will be contacted monthly to ensure intervention delivery and resolve any unforeseen technical difficulties. These follow-up calls are strictly for technical support and continued engagement, with no behavior change support provided. The case manager’s actions are guided by a comprehensive handbook that includes protocols for missing data transitions and threshold violations.

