#### Care as Usual

Participants randomly assigned to the care-as-usual group will receive standard care without any restrictions and will be allowed to seek additional care or assistance for lifestyle changes if needed. Participants in the control group will be asked to fill in questionnaires and undergo the same assessments as the intervention group.

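### Serious adverse events reach the trial by patient report or record finding, while only the intervention arm has regular contact in the first 6 months, so by-arm event counts may differ through capture alone

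*Protocol article*

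**What the plan says.** The Monitoring section sets the period and level of surveillance, "Throughout the study period, monitoring of serious adverse events will be performed per center", and the trigger for reporting: "If serious adverse events are reported by patients or discovered in the patient record, this will be reported to the sponsor". The rule has two routes and does not differ by arm. The sponsor then registers the events with the authorities.

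The section on the case manager's role describes extra contact for app users. At the start: "Within the first week after inclusion, the case manager will contact the participants to verify proper installation of the app and monitoring devices". After that: "During the intervention period (6-month follow-up), patients will be contacted monthly to ensure intervention delivery and resolve any unforeseen technical difficulties". The purpose of these calls is limited: "These follow-up calls are strictly for technical support and continued engagement, with no behavior change support provided". The TIMELY App section adds a diary, "ecological momentary assessment diary assessment of symptoms, perceived stress, sleep quality". The Clinical Dashboard section adds automatic tasks for case managers when symptoms are reported or blood pressure deviates. Case managers may phone patients for safety reasons and check each new exercise prescription on Mondays.

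For controls, the Care as Usual section says: "Participants in the control group will be asked to fill in questionnaires and undergo the same assessments as the intervention group". Under Study Procedure these shared assessments are an online questionnaire at 3 months and hospital visits at 6 and 12 months.

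**The concern.** Both SAE routes wait for something to happen: a patient mentions an event, or someone comes across it in the record. Under such a rule, the number of events found depends partly on how often staff and patient are in touch. In the first 6 months that frequency differs by design between the arms, and neither researchers nor participants are blinded.

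The likely direction is more recorded events under intervention at equal true risk. That could make a program with weekly exercise progression look less safe than it is, or hide a real reduction in events. Event data by arm also matter beyond the safety table: the Discussion says the cost-effectiveness analysis will count benefits from fewer future events, without saying where those event data come from.

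**Working it through.** The article gives no SAE rate, no capture share and no by-arm safety figure, so there is nothing of its own to reproduce. The check has two parts.

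**Contact opportunities in months 0 to 6**

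- Intervention: 1 first-week contact + 6 monthly contacts (monthly for 6 months) = 7 case-manager contacts, plus the 6-month visit, the 3-month online questionnaire, the diaries and the alerts.
- Control: the 6-month visit and the 3-month online questionnaire.
- Either arm: up to 3 reminder calls for late questionnaires.
- Months 6 to 12: the described contact is the same in both arms.

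**Illustration of the possible size**

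From the article: 180 and 178 randomized. Assumed: true risk *p*, equal in both arms; a share *r* of events found through the record, equal in both arms; of the remainder, a share *s1* (intervention) or *s0* (control) found through patient report.

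- Capture: c1 = r + (1 − r)·s1 and c0 = r + (1 − r)·s0.
- Apparent risk ratio = c1/c0, which does not depend on *p*.
- Expected recorded events = 180·p·c1 and 178·p·c0.
- False-positive rate: chance that a two-sided 5% two-proportion z test (pooled variance under the null) rejects although the true risks are equal.

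With s1 = 0.9 and p = 0.10:

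| r | c1 | c0 (s0 = 0.5) | Ratio | Expected events | False-positive rate | Ratio if s0 = 0.7 |
|---|---|---|---|---|---|---|
| 0 | 0.90 | 0.50 | 1.80 | 16.2 vs 8.9 | 32% | 0.90/0.70 = 1.29 |
| 0.5 | 0.95 | 0.75 | 1.27 | 17.1 vs 13.4 | 10% | 0.95/0.85 = 1.12 |
| 0.8 | 0.98 | 0.90 | 1.09 | 17.6 vs 16.0 | 6% | 0.98/0.94 = 1.04 |
| 0.95 | 0.995 | 0.975 | 1.02 | 17.9 vs 17.4 | 5% | 0.995/0.985 = 1.01 |
| 1 | 1.00 | 1.00 | 1.00 | 18.0 vs 17.8 | 5% | 1.00 |

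The first row ignores the record route and is an outer bound, not a description of this trial. In that row the false-positive rate is 18% at p = 0.05 and 59% at p = 0.20.

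The table applies to events of the first 6 months. Over 12 months the ratio is diluted. If half the events fall after month 6 and both arms then report at s = 0.5, the ratio at r = 0.5 is (0.95 + 0.75)/(0.75 + 0.75) = 1.13, and at r = 0.95 it is (0.995 + 0.975)/(0.975 + 0.975) = 1.01.

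**The case against.** A reader might infer that the trial's safety comparison will be biased. The article does not support that, for four reasons.

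1. There is no such comparison in it. Safety is not among the primary or secondary outcomes, the Statistical Analysis section plans no between-arm SAE test, and the aim of fewer recurrent events is measured by a risk score rather than by event counts. This stands.
2. Patient report is only one of two routes. The record route covers both arms, and hospital admissions are the kind of event that records tend to show. This also stands, and it is why the effect may be negligible. One could reply that staff search harder after a prompt, or that admissions elsewhere never reach the center's record. Both are plausible, but the article says neither.
3. The monthly calls are for technical support and engagement, the Monday check is not a patient contact, and diaries record symptoms rather than SAEs. A control patient can mention an earlier admission at the 6- or 12-month visit, so the extra calls may change when an event is learned more than whether it is. This weakens the point without removing it: a patient phoned about missing data has an occasion to mention an admission that a control patient lacks.
4. A journal article condenses the protocol, and the ethics-approved full version may contain a common SAE query and a fixed record search. If so, the sponsor need only confirm it. The point rests on what is stated: event-triggered capture beside contact that differs by arm.

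Blinded analysis of outcome measures does not answer the point, because it acts after events have or have not been recorded.

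**Conclusion.** The unequal opportunity to report in months 0 to 6 is established from the text. An unequal count is only possible. Under the assumptions shown (equal true risk, equal record capture, reporting shares of 0.9 against 0.5 or 0.7), the apparent risk ratio for early events runs from about 1.01 or 1.02 when records find 95% of events to 1.12 or 1.27 when they find half. Record completeness decides between negligible and material, and the article does not give it. None of the assumed shares comes from the article.

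The two primary analyses, on the Coropredict score and the 6-minute walk test, are untouched. What is exposed is any SAE table by arm and any other use of event data by arm. This is a low-cost improvement to safety reporting, not a flaw in the main design.

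**What to change.** Recruitment is closed and 6-month follow-up is complete, so questions can no longer be added at 3 or 6 months. What remains feasible:

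- At the 12-month visits still to come (the article expects the last by May 2025), ask both arms the same structured question on hospitalizations and serious events since baseline.
- Apply one record check, with the same sources and the same window from baseline to 12 months, to all 358 randomized participants, except any who opted out and whose data must be deleted. If few visits remain, this check carries most of the weight.
- State in the analysis plan that by-arm SAE summaries rest on these common sources.
- List separately the events learned only through case-manager contact, and continue to report all events to the authorities as now.

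If the full protocol already provides a common query and record search, confirming that and saying so in the results paper is enough.

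The cost is modest extra record work at three centers, one question per remaining visit and one sentence in the analysis plan. The drawback is some recall error for events early in follow-up, which the record check should partly offset.

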### Dissemination Policy

The results of the TIMELY trial will be disseminated in academic and health care settings through scientific publications, symposia, and conference visits. Study participants will be informed about the results via a newsletter containing the highlights of the study outcomes. To reach a broader audience, local newspapers will be contacted to disseminate the results among the general public.

